### Interventions

Eligible patients will be randomised into one of three groups:
Patients in group A (Gp A) will receive a 15-min talocrural joint MT directed at the dorsiflexion before a 30-min specific task-oriented mobility and balance training 2 times per week. Further, a 20-min home-based ankle mobilisation and TOT programme 4 times per week, for 4 weeks.Patients in group B (Gp B) will receive a 45-min specific task-oriented mobility and balance training 2 times per week. Further, a 20-min home-based TOT programme 4 times per week, for 4 weeks.Patients in group C (Gp C) will receive no specific treatment.

All patients will receive their usual care involving appointments with the treating neurologist or other medical doctors and any medication such as anticoagulants or antihypertensive drugs. Interventions in groups A and B will be provided face-to-face by an experienced physiotherapist (KT). Patients will be asked to perform the home-based training on the intervention-free days only and given free choice of one rest day per week.

#### Manual therapy

MT will be carried out by an experienced physiotherapist who holds a Master’s degree in musculoskeletal physiotherapy (KT). MT will be performed according to American Academy of Orthopaedic Manual Physical Therapists guidelines [26] and directed towards the upper ankle joint structures and aim to increase the dorsiflexion ROM. Two different talocrural mobilisation techniques will be used. First, a talus on tibia technique at a Maitland joint mobilisation grade III will be employed on the submaximally dorsiflexed talocrural joint, followed by a grade I tibia distraction, alternated with anterior-posterior gliding. Second, a tibia on talus technique with a posterior-anterior force at a Maitland joint mobilisation grade III will be used on the submaximally dorsiflexed talocrural joint and combined with active forward-movements of the knee joint, followed by intermittent talocrural mobilisation ranging between Maitland grades III+ and III++, all of which are explained in detail in Fig. 2.

**Fig. 2 Fig2:**
[figure not shown]
Manual therapy techniques

#### Face-to-face task-oriented training

TOT will focus on activities involving mobility and dynamic balance. Activities will be based on the requirements of daily living, i.e. avoiding or stepping over obstacles or picking-up objects from the ground. Patients will be timed while being instructed to perform the goal-oriented activities with as much effort and speed as possible. The number of repetitions (or objects moved) will be counted aloud by the physiotherapist researcher as motivation. Additionally, patients will be encouraged to put maximum effort into the TOT, while remaining comfortable. According to established principles of motor learning, exercises should progress in difficulty taking into account the skill level of the task performer and the condition, under which it is performed [27]. Moreover, patients can choose the task order from a predefined list. Between tasks, patients may rest for 45–60 s. Table 1 presents an intervention chart based on the template for intervention description and replication (TIDieR) checklist [28]. Detailed information on the face-to-face and home-based intervention is provided in Additional file 2.

**Table 1 Tab1:** Intervention chart

Item no.	Item description		
**1 Brief name**	**Group A**	**Group B**	**Group C**
	Upper ankle joint manual therapy (MT) and task-oriented mobility and balance training (TOT)	Task-oriented mobility and balance training (TOT)	Control group: no intervention
**2 Why**	To evaluate the feasibility of the methods of a larger trial and explore the preliminary effects of a specific TOT versus its combination with talocrural MT on balance, mobility, ankle range of motion (ROM), number of falls and health-related quality of life in people post stroke.		
**3 What materials**	- Information sheet on study procedures - Information booklet on home-based TOT programme - Exercise diary including a compliance checklist		
**4 What procedures**	- Usual care		
	- TOT introduction: in lay language; description of the principles - Supervised TOT performance - Home-based TOT		
	- MT introduction: in lay language; description of the principles - MT performance of the talocrural joint - Home-based ankle mobilising exercise		
**5 Who provides**	The intervention will be provided by a trained physiotherapist who holds a Master’s degree in musculoskeletal physiotherapy and is studying for another Master’s degree in neurological physiotherapy		

#### Home-based training

The same home-based TOT programme will be used for patients in groups A and B. Patients will be informed they may select the TOT type and order but should alternate tasks over the intervention period. Selected tasks (T) should be performed for 2 min each in sets of 3, e.g. (T2+T5+T7+T8)*3. A 1-min pause will be scheduled between the various tasks, but not between sets of the same task. Patients will be trained carefully by the treating physiotherapist and their exercise performance supervised and adapted weekly. Gp A will receive a self-mobilisation technique of the upper ankle joint. Patients will be instructed to commence their training with self-mobilisation. Patients in Gp B will perform another task-oriented exercise. Patients will be instructed to record their training in an exercise diary, e.g. number of repetitions/time period. Similar to face-to-face training, training will progress in difficulty (Additional file 2).

#### Strategies to improve adherence to interventions

A 4-week goal-oriented face-to-face intervention will be used. Goal setting and supervision of exercises by a physiotherapist have been shown to facilitate adherence [29]. The study intervention will be based on ADL relevant to people post stroke which may enhance adherence. In addition, the described TOT could be motivating for patients. The 1:1 treatment sessions will be scheduled at the patients’ convenience.

As for home-based training, simple exercise instructions written in lay language and including photos will be employed to guide and improve training adherence. Patients will be allowed to freely choose the time, task order and type; however, all tasks should be trained. Tasks will be demonstrated and explained by the physiotherapist. The scheduled duration of the home-based training is 20 min, likely perceived doable by patients. An exercise diary with a compliance checklist will be used to monitor adherence and checked by the physiotherapist weekly throughout the intervention period. Patients will be reminded of their post-intervention and follow-up appointments.

### Data collection

Demographic (gender, age) and stroke-specific data (lesion side; disease duration; modified Rankin scale score) will be extracted from patients’ charts at eligibility screening (−*t*_1_). Study-specific assessment data will be collected at baseline (*t*_1_), post-intervention (*t*_2_) and follow-up (*t*_3_) at 4 weeks after completion (Table 3) by two physiotherapists blinded to the study intervention. Assessments will be performed at similar times to increase comparability. In addition to ROM measurement, the validated German version of all assessments will be used. Semi-structured interviews will gather in-depth information regarding acceptance of the study intervention. Changes from baseline and from post-intervention will be evaluated for all outcomes using means, medians, proportions and text as appropriate.

#### Primary outcome and outcome measures

##### Feasibility

*Recruitment, retention and adherence rates*

The feasibility of conducting a full-scale RCT will be explored using predefined criteria, recording monthly recruitment and adherence rates to the face-to-face intervention. Using an exercise diary, adherence to the home exercise programme and any non-adherence will be recorded, including reasons (e.g. discontinuation due to lack of interest or injury). Any non-retention will also be recorded with reasons (e.g. consent withdrawn) (Fig. 1).

The criteria for feasibility success will be:
a target recruitment rate of 25% of 145 eligible patients (or 6 patients per month). The number of 145 was estimated according to information received from neurologists and clinicians practising within 30 km of the study centre, concerning the number of eligible chronic stroke patients they have treated within the previous 9 months,a target retention rate of 85%,a target minimum adherence rate of 75% for face-to-face interventions (6 practice sessions out of a maximum of 8) anda target minimum adherence rate of 75% for home-based interventions (12 practice sessions out of a maximum of 16).
b.*Compliance with the home exercise programme*

An exercise diary will be used to report compliance. Patients in groups A and B will be asked to complete an exercise diary to record type order and repetitions performed of chosen exercises. They should also explain any problems or deviations from the home exercise protocol.
c.*Adverse events and falls*

Falls are considered a relevant outcome from a mobility and balance intervention study because of the associated injury risk. Any adverse events and side effects will be systematically recorded and evaluated using a formal log including the type of adverse event, dates, severity, causality differentiated into serious/non-serious, actions to restore or improve the patient’s wellbeing and outcome of the event. A falls log will be provided to patients, which will be collected at *t*_2_ and *t*_3_, in addition to the number of and reasons for falls within prior 6 months. Study-related adverse events such as training-related injuries will be treated and paid for. Severe adverse events will lead to early study termination.
d.*Acceptability of the intervention*

Acceptability of the intervention will be assessed using semi-structured qualitative interviews comprising four predefined questions presented in Table 2, utilised to learn how the interventions worked for the patients and how well they were appreciated. This is of clinical relevance because high acceptability may help increase motivation, autonomy and adherence in patients.

**Table 2 Tab2:** Semi-structured interview guide

Introduction	
Main part	
Question #1	Would you please describe your experiences with the training in this study?
Question #2	Is there anything that would motivate you to further participate in this training (i.e. after the study)?
Question #3	What do you think about continuing with the home-exercise programme?
Question #4 (Gp A)	How did you experience the manual therapy of your foot?
Question #4 (Gp B)	How was the duration of the training for you?
Prompt #1	Why so?
Prompt #2	Could you describe this in more detail?
Thanks and conclusion	Many thanks for participating in this interview.

Adapted from [30, 31]

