The research question is as follows: Is a full-scale RCT feasible to investigate the effects of specific TOT versus its combination with talocrural MT on balance, mobility, ankle ROM, number of falls and HRQoL, based on the feasibility criteria of recruitment, retention and adherence rates, compliance, adverse events, falls and acceptability of the intervention? The null hypothesis is that a larger main study need not be performed.

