### Data analyses

#### Statistical analysis

IBM SPSS Software, release 26.0 (IBM Corporation, Armonk, NY, USA) and GraphPad Prism 8, San Diego, CA, will be used for the data analyses. Statistical significance will be defined as a two-tailed *p*-value <0.05. The percentage of missing data will be recorded. Using Little’s test of missing completely at random (MCAR) [55], the data will be checked, signified by a *p*-value >0.05. An intention-to-treat analysis will be performed.

Descriptive statistics will be used for the baseline demographic variables, primary and secondary outcomes. Continuous data will be checked for normal distribution using the Shapiro-Wilk Test, Q-Q plots and histograms. Raw count (number (*N*), %) will be presented for counted (*N* females and males, *N* falls and *N* adverse events if any), compliance (types and order of home exercises, *N* of repetitions and deviations from the protocol) and nominal data (gender, recruitment, retention and adherence rates). Medians (range; 25th and 75th percentiles) will be reported for ordinal data (Mini BESTest if there are missing data, SIS); mean (95% confidence interval (CI)) will be reported for continuous data (age, Mini BESTest if data can be transformed into interval level, 10MWT, TUG, TUG_manual_, TUG_cognitive_, ankle ROM measures).

The recruitment rate (%) will be estimated by dividing the number of consenting patients by the *N* of eligible patients, multiplied by 100. The retention rate determined by dividing the *N* of patients who completed the study by the *N* of the total sample, times 100. Adherence rates will be calculated by dividing the *N* of TOT sessions (8x; 16x) performed by the patients, divided by the *N* of the scheduled (face-to-face; home-based) training sessions over the 4-week study period, times 100 [56]. The eligibility, recruitment and adherence rates will be calculated with their 95% CI according to the Wilson “score” method cited by Newcombe [57]; when the proportion is close to 0 or 1, a Poisson approximation as described by Brown and colleagues will be used [58].

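### The adverse-event log gives causality the categories of seriousness, and the termination sentence leaves open whether one patient or the whole trial stops

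*Protocol article*

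**What the plan says.** The research question in the Introduction asks whether a full-scale trial is feasible "based on the feasibility criteria of recruitment, retention and adherence rates, compliance, adverse events, falls and acceptability of the intervention". Study design and location repeats adverse events as part of the primary outcome.

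The Feasibility section, under adverse events and falls, describes a formal log. Its items are event type, dates, severity, then "causality differentiated into serious/non-serious", then the actions taken and the outcome of the event. Two rules follow directly:

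- "Study-related adverse events such as training-related injuries will be treated and paid for".
- "Severe adverse events will lead to early study termination".

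Under Interventions, groups A and B receive study training and group C receives none; all three groups keep their usual care. The Statistical analysis section plans counts of adverse events and says "An intention-to-treat analysis will be performed".

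**The concern.** Two sentences do not work as printed.

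First, serious and non-serious are not categories of causality. A log filled in that way has a severity entry and a seriousness entry, but nothing that says whether the training caused the event. For a pilot that is to judge whether manual therapy and intensive balance training can go forward to a larger trial, relatedness is the most useful thing the log can record.

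Second, the termination sentence has no condition on relatedness, arm or number of events, and its scope can be read two ways. If it means the trial, one unrelated event could end the pilot before it answers its question. If it means the patient, it does not say whether assessments stop along with training, and that decides whether the patient's later data reach the intention-to-treat analysis.

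**Working it through.** **Check 1: the log categories.** Three different attributes of an adverse event are involved.

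| Attribute | Question it answers | Suitable categories | In the printed log |
|---|---|---|---|
| Severity | How intense was it? | grades of intensity | listed as its own item |
| Seriousness | Does it count as a serious event? | serious / non-serious | not named, but its categories appear |
| Causality | Was it related to the intervention? | related / unrelated | named, but with the categories of seriousness |

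Severity has its own place in the list, so the phrase cannot be read as a description of severity. No other section of the article gives categories for causality.

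Take two minor ankle sprains, one during a supervised session and one unrelated to any training. Coded as printed, both are entered under causality as non-serious and are indistinguishable on that field. Yet "Study-related adverse events such as training-related injuries will be treated and paid for" needs exactly that distinction. The paragraph therefore assumes a judgement that its own categories do not capture.

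**Check 2: the termination sentence.** The two rules stand next to each other. The one on treatment and payment is limited to study-related events. The one on termination is not. It sets no number of events and no arm.

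- *Whole-trial reading.* Taken literally, a single severe event of any cause in group A, B or C stops the pilot.
- *Patient-level reading.* The affected patient stops. Whether the *t*2 and *t*3 assessments also stop is not stated. If they do, that patient's later outcomes are missing from the intention-to-treat analysis; if they continue, nothing is lost.

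**Illustration of the whole-trial reading.** The planned sample is 36, and the article's attrition formula reproduces its larger figure: 36 / (1 − 20/100) = 36 / 0.80 = 45. The article gives no rate of severe events, so the per-patient risk *p* over the study is an assumption, taken as equal and independent across patients. The chance of at least one such event is 1 − (1 − *p*)^n.

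| Assumed *p* | n = 36 | n = 45 |
|---|---|---|
| 0.5% | 0.165 | 0.202 |
| 1% | 0.304 | 0.364 |
| 2% | 0.517 | 0.597 |
| 5% | 0.842 | 0.901 |
| 10% | 0.977 | 0.991 |

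For example, at 1% and n = 36: 1 − 0.99^36 = 0.304. The table shows only that a rule triggered by one event of any cause need not be remote in its effect. It is not an estimate for this trial.

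**The case against.** The strongest reply is that both sentences are slips of condensation. The causality phrase is probably a merged list item. Causality is named as a log item, and relatedness is plainly intended, because the paragraph acts on study-related events. The log form and the full protocol, version 1.3, are not shown and may be correct. This stands in part. A reader might infer that the trial will fail to record relatedness; the article does not support that, because the form may differ from the printed sentence. Nor is the absence of definitions or of a named decision-maker a finding. What remains is that the published text pairs the wrong words, and nothing else in it corrects them.

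The second reply is that stopping after any severe event, whatever its cause, is a sound safety rule for a patient. Eligibility requires confirmation that active training is not contraindicated, and a new stroke or a fracture could remove that condition without being caused by the training. This stands. It would go too far to say that patient-level stopping must be limited to related events; that is a clinical choice. The relatedness condition matters for a whole-trial stop.

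Three further inferences should be resisted:

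- That the sentence names nothing to be terminated. It names the study; only the scope is unclear.
- That "discontinuation due to lack of interest or injury" settles the patient-level reading. That phrase illustrates reasons for not adhering to the home programme, not exit from the study.
- That the retention target, or the share of patients in the untreated arm, measures the harm. Both are the same however these sentences are worded.

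**Conclusion.** The point holds as a minor correction to two sentences. The causality categories are wrong as printed; this rests on the text alone. The termination sentence is ambiguous in scope and, on its literal whole-trial reading, could end the pilot for one event unrelated to the intervention. Which reading the investigators intend cannot be determined from the article.

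No effect on the results can be quantified, because no event rate is given and none of the listed success criteria sets an adverse-event threshold. Sample size, power, significance level and the recruitment, retention and adherence targets are unaffected. The practical consequences are conditional: relatedness goes unrecorded if the form copies the printed wording, and later data are lost if termination of a patient also ends assessment.

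**What to change.** Reword the two sentences.

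1. *Log.* List severity, seriousness (serious / non-serious) and causality (related / unrelated to the study intervention) as three separate fields, completed in all three arms. Report adverse events by arm and relatedness.
2. *Termination.* State that a severe or serious adverse event ends that patient's training where continuing is judged unsafe, and that the *t*2 and *t*3 assessments continue where possible so that the patient stays in the intention-to-treat analysis. State separately that the whole trial stops only for intervention-related serious events, at a threshold that the investigators set.

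The cost is two sentences and, if the form follows the printed wording, one column split in two. In that case, events already logged would need a relatedness judgement added. The planned adverse-event counts gain one breakdown; the sample size and the outcome analyses do not change.

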#### Other secondary outcomes and outcome measures

Patients may use their walking aid for all walking tests, but this needs to be documented and used consistently for all trials.
*Walking speed (10-m walk test, 10MWT)*

The 10MWT at maximum speed will be used as a functional measure of walking. It has been recommended by various task forces [34, 35]. Academy of Neurologic Physical Therapy test instructions will be followed [36] and data recorded in m/s. The average will be calculated from two trials.

For the 10MWT, an excellent concurrent validity has been shown with ADL [37]. Good convergent validity with the 6-min walk test [38] has been observed, an excellent interrater and test-retest reliability and a minimal detectable change (MDC) of 16% [39].
b.*Functional mobility (Timed Up and Go, TUG)*

The TUG [40] is a measure of functional mobility able to detect change over time in patients post stroke [39]. The patient is observed and timed while he or she rises from a chair with armrests, walks 3 m as quickly and safely as possible towards a marking, turns, walks back and sits. Excellent interrater reliability has been found, plus good convergent validity with relevant measures [40]. The MDC of the TUG in stroke patients is 23% [39].
c.*Functional mobility with dual tasking (TUG*_*manual*_
*and TUG*_*cognitive*_*)*

Dual tasking will be assessed using the TUG_manual_ and TUG_cognitive_ where the TUG is combined with a motor (carrying) or cognitive task (subtracting in threes) [41]. For both dual-tasking TUGs, a good test-retest reliability and convergent validity have been confirmed [42, 43]. An MDC of 3.53 s for the TUG_manual_ [42] has been observed in people after stroke. The time difference between the TUG and TUG_cognitive_ is indicative of an increased fall risk [44].
d.*Ankle range of motion (passive and active dorsiflexion and plantarflexion ROM)*

Ankle mobility will be assessed using different techniques to assess the effects of MT.
*Non-weight-bearing dorsiflexion and plantarflexion ROM measurement*

Passive and active talocrural dorsiflexion (DF) and plantarflexion (PF) ROM will be assessed in non-weight-bearing supine position with the knees on a standard knee roll (20° flexed), to avoid tensioning of the gastrocnemius muscle [45]. A standard measurement technique is described in detail in Additional file 3. Data will be recorded using the neutral-zero method [46]. Excellent interrater reliability has been demonstrated for ankle dorsiflexion [45] and plantarflexion measures [47].
2.*Weight-bearing dorsiflexion ROM measurement*

Ankle dorsiflexion ROM will also be assessed utilising a tape measure and a weight-bearing lunge facing a wall, as validated by Konor et al. (2012) and outlined in detail in Additional file 3 [48]. Excellent interrater [49] and intrarater reliability, low measurement error and an MDC of 1.1–1.5 cm has been demonstrated for this measurement technique [48].
e.*Disability and HRQoL after stroke (Stroke Impact Scale, version 2.0, SIS v2.0)*

The validated German version [50] of the SIS v2.0 [51] will be used to assess disability and HRQoL. The SIS is a stroke-specific PROM comprising 64 items and assessing 8 domains (strength, memory, emotion, communication, ADL and instrumented ADL (IADL), mobility, hand function, and social participation). A summary score is not calculated, but a physical domain score can be created from the strength, hand function, mobility and ADL/IADL domains. In the emotion domain, items 3a-e and 3g are reverse scored, with all items scored on a 5-point Likert scale. Scores for each domain are transformed to a 0–100 score with lower scores representing poor HRQoL; using the formula: Transformed Scale = [(Actual raw score - lowest possible raw score)/Possible raw score range] × 100. In addition, the SIS v2.0 includes a 0–100 visual analogue scale, with 0 representing no recovery and 100 representing full recovery.

Moderate to excellent internal consistency, test-retest reliability, convergent, divergent and discriminant validity have been demonstrated for the SISv2 [51].

